### 2.13. Electromyography

After receiving the participant, all hairs in the area where the electrodes will be placed will be shaved. The skin must be cleaned with alcohol and abrasive paste (ANVISA Registration: 81210770020) before attaching the electromyography (sEMG) electrodes to ensure proper contact. Disposable active bipolar electrodes with silver/silver chloride contact (Ag/AgCl, Double Trace LHED4020, Shanghai Litu Medical Appliances Co., Ltd., Shanghai, China, ANVISA Registration: 8035169000) will be used, each with a diameter of 1 cm for the circular conductive area and a spacing of 2 cm between the centers. All data collection involving electromyography will follow the current recommendations proposed by [26,27].

Regarding the proposed task, the research context will be characterized by a laboratory environment, which will follow the same tasks proposed in the posturography and maximal voluntary isometric contraction section, which will be performed in a counterbalanced manner (Latin square technique) with a 2 min interval between tasks. The electrodes will be positioned on both limbs along the axes of the muscle fibers:

Medial Gastrocnemius (GM): Proximal and posterior part of the medial condyle and adjacent part of the femur, maintaining a suggestive distance of 20 mm between the electrodes. The electrodes should be positioned over most of the muscle belly (SENIAM/ISEKI) [27].

Anterior Tibial (TA): Lateral condyle and proximal half of the lateral surface of the tibia, interosseous membrane, deep fascia, and lateral intermuscular septum, maintaining a suggestive distance of 20 mm between the electrodes. The electrodes should be positioned at 1/3 of the line between the tip of the fibula and the tip of the medial malleolus (SENIAM/ISEKI) [27].

### 2.14. Posturography

For the analysis of postural control, a force platform (AccuSway PLUS, AMTI, Watertown, USA) will be used, on which participants must remain in an orthostatic position, barefoot, with their upper limbs positioned along their body. Three distinct positions will be applied: (i) participants will remain with their feet parallel, approximately hip-width apart; (ii) semi-tandem condition, in which the feet will also be parallel and hip-width apart, but with the dominant foot positioned behind the non-dominant foot, aligning the heel of the anterior foot with the plantar arch of the posterior foot; and (iii) tandem condition, in which the non-dominant foot will be positioned in front of the dominant foot. In all conditions, participants must keep their eyes open and are instructed not to move their head, arms, or torso during the task. Each condition will be performed for 60 s. Between each task, there will be a two-minute rest interval to minimize the effect of fatigue on the results. The displacement of the center of pressure (COP) will be estimated from ground reaction forces and force moments captured by the force platform. The raw data will be digitized with a sampling frequency of 50 Hz, subjected to a 5 Hz low-pass filter, and stored for later analysis. Standardization of positions aims to ensure greater consistency between measurements, minimizing variations in foot placement that could interfere with the accuracy of the results. In addition to the posturographic assessment, surface electromyographic (sEMG) signals will be collected bilaterally from the medial gastrocnemius (GM) and anterior tibial (TA) muscles to analyze muscle activation patterns and synergism between the dominant and non-dominant lower limbs, as well as the neuromuscular contribution in the different proposed conditions [27].

### 2.15. Data Management

The original data will be digitized as image files by a trained research assistant and subsequently reviewed by a second team member. All digital records will be securely stored on a password-protected computer. To ensure data integrity, a double-entry process will be implemented using automated validation procedures in a Microsoft Excel spreadsheet (Microsoft Corporation, Redmond, WA, USA), conducted remotely by an independent reviewer. Any discrepancies identified during this process will be resolved through direct comparison with the original documents.

### 2.16. Statistical Analysis

Sample size calculation

An a priori sample size calculation was performed using G*Power software (v. 3.1.9.6) [28]. A conservative medium omnibus effect size (Cohen’s f = 0.25) was adopted, consistent with methodological guidance for a priori estimation in strength and conditioning/exercise research [29]. Assuming α = 0.05, power (1 − β) = 0.80, and three parallel groups, the required total sample size for an omnibus ANOVA comparison is 159 participants (53 per group). To account for potential losses to follow-up of up to 20%, the planned recruitment target was increased to 192 participants (64 per group), ensuring adequate power for the primary analyses. Participants of both sexes, over 60 years of age (M01.060.116.100), participating in the Open University for the Elderly program at Augusto Motta University (UNATI/UNISUAM), will be included.

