### 2.11. Concern About Falling

Concern about falling will be assessed using the Falls Efficacy Scale-International, Brazilian version (FES-I-Brazil). This questionnaire presents questions about the perception of fear of falling when performing 16 activities. Each activity has a score from one to four, with 1 point (not at all concerned), 2 points (slightly concerned), 3 points (moderately concerned), and 4 points (extremely concerned). The total score can range from 16 to 19 points (low concern), 20 to 27 points (moderate concern), and 28 to 64 points (high concern). This instrument will be administered at baseline and within 48 h after the final intervention session [16,17,18]. In addition to analyzing FES-I as a continuous outcome within the planned Group × Time framework, interpretability will be supported by reporting the proportion of participants who shift across established concern categories (low/moderate/high) from baseline to post-intervention. Because MCID/MID thresholds for patient-reported outcomes can vary substantially across estimation methods and populations, and because credible anchor-based MIDs are not consistently available for community-dwelling older adults, the study will also apply a transparent distribution-based benchmark (0.5 baseline SD) to describe a minimal important change in FES-I as a supplementary interpretive reference rather than a substitute for the primary inferential model [23,24]. This approach is intended to strengthen clinical interpretability while avoiding overstatement of “clinical significance” in the absence of stable, population-specific anchor-based thresholds.

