### 2.17. Data Analysis

Descriptive statistics will be presented as mean ± standard deviation for continuous variables and as frequency (percentage) for categorical variables. Distributional assumptions will be evaluated using Shapiro–Wilk tests and visual inspection (histograms and Q–Q plots), and homogeneity of variance will be examined (e.g., Bartlett/Levene, as appropriate). Because the trial includes three groups and two time points (baseline and post-intervention), the primary inferential objective for each outcome will be to test the Group × Time interaction, which directly evaluates whether pre–post changes differ between groups.

For outcomes meeting parametric assumptions, a mixed-design model will be applied with Group (A, B, C) as a between-subject factor and Time (baseline, post-intervention) as a within-subject factor. The main effect of Group, main effect of Time, and, critically, the Group × Time interaction will be reported. Because Time has only two levels, sphericity is not applicable. If the interaction is statistically significant, planned follow-up comparisons (simple effects) will be conducted to compare: (i) pre–post change within each group and/or (ii) between-group differences at each time point, using multiplicity-adjusted procedures (see below).

If parametric assumptions are violated, outcomes will be analyzed using an appropriate robust repeated-measures approach (e.g., transformation where suitable, or mixed-model estimation with robust standard errors), preserving the Group × Time framework. In all cases, inference will be centered on the interaction term as the test consistent with the study design.

Multiplicity control: The primary outcome (FES-I) will be tested at α = 0.05 (two-sided). Secondary outcomes will be interpreted as supportive/exploratory and will include multiplicity control to reduce false-positive risk across the outcome family. For post hoc/simple-effects contrasts following a significant interaction, *p*-values will be adjusted (e.g., Holm–Bonferroni). For multiple secondary outcomes, an additional correction strategy will be applied (e.g., false discovery rate control) to maintain interpretability across the secondary endpoint set.

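### The target of 192 does not cover the stated 20% loss: it was reached by multiplying by 1.2 instead of dividing by 0.8, and power at that loss is about 79%, not 80% (minor)

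*Protocol article*

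**What the plan says.** The sample size paragraph in section 2.16 of the protocol article makes four linked statements.

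- Effect size: "A conservative medium omnibus effect size (Cohen’s f = 0.25) was adopted".
- Error rates and design: "Assuming α = 0.05, power (1 − β) = 0.80, and three parallel groups". Section 2.17 confirms the significance level for the primary outcome: "The primary outcome (FES-I) will be tested at α = 0.05 (two-sided").
- Requirement before losses: "the required total sample size for an omnibus ANOVA comparison is 159 participants (53 per group").
- Allowance for losses and the conclusion drawn: "To account for potential losses to follow-up of up to 20%, the planned recruitment target was increased to 192 participants (64 per group"), with the target described as "ensuring adequate power for the primary analyses".

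The abstract and sections 2.1 and 2.6 repeat the 192. No section gives another loss rate or another basis for the step from 159 to 192.

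**The concern.** If a fraction d of those recruited is lost, then n / (1 − d) must be recruited to keep n. Multiplying by (1 + d) gives too few, because the loss applies to the larger recruited number and not to n. A target of 192 against a requirement of 159 looks like the second calculation.

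What is at stake is whether a stated property of the design is true. The paragraph gives the requirement, the loss rate and the target, and concludes that power is secured. If the three figures do not support that conclusion, the results paper will probably repeat a power statement that any reader can refute from the same paragraph.

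**Working it through.** **Inputs, all from section 2.16:** f = 0.25, α = 0.05, power 0.80, three groups, 159 required (53 per group), loss up to 20%, target 192 (64 per group). Equal allocation is stated in section 2.1.

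**Step 1. Reproduce the 159.** For a one-way ANOVA with k = 3 groups, power = P(F′ > F crit), where F′ is noncentral F with 2 and N − 3 degrees of freedom and noncentrality λ = N f².

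| N | λ = N × 0.0625 | Power |
|---|---|---|
| 157 | 9.81 | 0.799 |
| 158 | 9.88 | 0.802 |
| 159 | 9.94 | 0.805 |

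The smallest N reaching 0.80 is 158. With equal groups it is 159. The protocol's figure reproduces.

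**Step 2. Find where 192 comes from.**

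- Multiplying per group: 53 × 1.2 = 63.6, rounded up to 64; 64 × 3 = 192. This matches.
- Multiplying the total: 159 × 1.2 = 190.8, rounded up to 191. This does not match, so the rounding was evidently done per group.
- Dividing per group: 53 / 0.8 = 66.25, rounded up to 67; 67 × 3 = 201.
- Dividing the total: 159 / 0.8 = 198.75, rounded up to 199.

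Only multiplication by 1.2, per group, gives 192. The balanced number that covers 20% loss is 201, nine more than planned (three per group). Check: 201 × 0.8 = 160.8, which is at least 159.

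**Step 3. What 192 leaves at 20% loss.** 192 × 0.8 = 153.6, or 64 × 0.8 = 51.2 per group. That is about 153 completers (51 per group), five to six short of 159.

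**Step 4. Power at that number, by the formula in step 1.**

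| Situation | N | Power at f = 0.25 |
|---|---|---|
| 192 recruited, no loss | 192 | 0.878 |
| Protocol's requirement | 159 | 0.805 |
| 192 recruited, 20% lost, 153.6 rounded up | 154 | 0.791 |
| 192 recruited, 20% lost, 51 per group | 153 | 0.788 |

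**Step 5. The loss that 192 does cover.** 1 − 159/192 = 33/192 = 0.172. The target keeps 159 completers up to 17.2% loss, which is 11 of 64 per group.

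**The case against.** The best argument on the other side is about size. The protocol speaks of losses up to 20%, so 20% is a ceiling. For any loss up to 17.2% the target leaves at least 159 completers, and with no loss power is 0.88. Even at the ceiling the gap to 80% is 1.2 percentage points (0.800 − 0.788). All of this stands, and it is why the point is minor. It does not make the sentence correct, because the ceiling is the case the sentence claims to cover.

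A second argument is that section 2.17 keeps participants with incomplete follow-up in the model under a missing-at-random assumption, so they are not wholly lost. This helps little. The primary test is the Group × Time interaction over two time points, and a participant with a baseline value only says little about pre–post change.

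A reader might also go further and infer that f = 0.25 is too large to be called conservative, because it implies a difference above the 0.5 SD reference in section 2.11. The documents do not support that. On the scale of the analysed change, f = 0.25 corresponds to 0.25 / √(2/9) = 0.53 SD between control and both vibration arms if those two are equal, or 0.25 × √6 = 0.61 SD between the extreme arms if the three are evenly spaced. The reference in section 2.11 is a "distribution-based benchmark (0.5 baseline SD"), which is a different unit. Assuming equal SDs at both visits and pre–post correlation r, the SD of change is √(2(1 − r)) baseline SDs. The implied difference therefore exceeds 0.5 baseline SD only if r is below about 0.56 (equal vibration arms) or 0.67 (evenly spaced). The protocol gives no r. It also offers the benchmark as a supplementary aid to interpretation, not as the difference the trial is sized to detect.

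**Conclusion.** The statement is wrong as written, and the error is minor. At the stated 20% loss, 192 leaves about 153 completers against a requirement of 159, and omnibus power for f = 0.25 is about 79%, not at least 80%. The target supports the 80% claim only up to about 17% loss.

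The inference that the trial is seriously underpowered would not be justified. The shortfall is about one percentage point and arises only near the top of the stated loss range.

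The figures assume that losses are spread evenly over the three groups and that lost participants contribute nothing to the test. They also refer to the one-way omnibus ANOVA used for sizing. They carry over to the Group × Time test if f = 0.25 is read on the scale of pre–post change. On another scale, power would depend on a pre–post correlation that the protocol does not state. That is a separate question and does not alter the inflation error.

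**What to change.** Keep 192 and correct the sentence in section 2.16, for example:

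> 192 participants (64 per group) allow for up to 17% loss to follow-up at 80% power; at 20% loss (about 153 evaluable) power is about 79% for f = 0.25.

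This costs one sentence and no participants. The abstract and sections 2.1 and 2.6, including the 192 prepared allocations, stay as they are. The only price is that the stated figure becomes slightly less favourable.

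If the team prefers to keep the 20% allowance at 80% power, the balanced target is 201 (67 per group). That means nine more participants, a longer allocation list and a change wherever 192 appears. A gain of about one percentage point does not require it.

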### 2.17. Data Analysis

Descriptive statistics will be presented as mean ± standard deviation for continuous variables and as frequency (percentage) for categorical variables. Distributional assumptions will be evaluated using Shapiro–Wilk tests and visual inspection (histograms and Q–Q plots), and homogeneity of variance will be examined (e.g., Bartlett/Levene, as appropriate). Because the trial includes three groups and two time points (baseline and post-intervention), the primary inferential objective for each outcome will be to test the Group × Time interaction, which directly evaluates whether pre–post changes differ between groups.

For outcomes meeting parametric assumptions, a mixed-design model will be applied with Group (A, B, C) as a between-subject factor and Time (baseline, post-intervention) as a within-subject factor. The main effect of Group, main effect of Time, and, critically, the Group × Time interaction will be reported. Because Time has only two levels, sphericity is not applicable. If the interaction is statistically significant, planned follow-up comparisons (simple effects) will be conducted to compare: (i) pre–post change within each group and/or (ii) between-group differences at each time point, using multiplicity-adjusted procedures (see below).

If parametric assumptions are violated, outcomes will be analyzed using an appropriate robust repeated-measures approach (e.g., transformation where suitable, or mixed-model estimation with robust standard errors), preserving the Group × Time framework. In all cases, inference will be centered on the interaction term as the test consistent with the study design.

Multiplicity control: The primary outcome (FES-I) will be tested at α = 0.05 (two-sided). Secondary outcomes will be interpreted as supportive/exploratory and will include multiplicity control to reduce false-positive risk across the outcome family. For post hoc/simple-effects contrasts following a significant interaction, *p*-values will be adjusted (e.g., Holm–Bonferroni). For multiple secondary outcomes, an additional correction strategy will be applied (e.g., false discovery rate control) to maintain interpretability across the secondary endpoint set.

Missing data: Analyses will follow an intention-to-treat principle. Missing outcome data will be described (extent, pattern, and reasons when available). The primary repeated-measures models will be implemented using estimation procedures that allow inclusion of participants with incomplete follow-up (under a missing-at-random assumption). If missingness exceeds a minimal threshold or appears differential by group, sensitivity analyses will be performed (e.g., multiple imputation and/or complete-case/per-protocol comparisons).

All analyses will be performed in SPSS (Version 21, Chicago, IL, USA), with the significance threshold set at α = 0.05.

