The seated intervention group (Group C) will follow the same routine of physical activities and undergo SVT in a seated position on a 30 cm high chair, with knees flexed at 120° and hands resting on the thighs in a comfortable posture, simulating the joint angles of the semi-squat protocol. The vibration parameters will be the same as those used for Group B.

Initial assessments will be conducted before randomization and before the start of the intervention period. Post-intervention assessments will be conducted within 48 h after the last intervention session, preferably at the same time as the initial assessment, in order to minimize possible circadian variations and effects related to fatigue. The same sequence of assessments will be maintained for all participants: (1) the Falls Efficacy Scale-International (FES-I, Brazilian version) to assess concern about falling; (2) the 2 min stationary march test to assess functional physical fitness; (3) bilateral surface electromyography (sEMG) of the tibialis anterior and medial gastrocnemius muscles using the EMG832C system (EMG System do Brasil, São Paulo, Brazil); and (4) posturography performed simultaneously with sEMG using a force platform (AccuSway PLUS, AMTI, Watertown, MA, USA).

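### The primary FES-I test is valid but does not use the pre-randomisation baseline efficiently, and its effect scale is left to assumption checks; one baseline-adjusted model in FES-I points would settle both

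*Protocol article*

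**What the plan says.** The Introduction defines the primary endpoint as the change in FES-I from baseline to post-intervention. Section 2.17 (Data Analysis) makes the Group × Time interaction the primary inferential objective for every outcome. For outcomes that meet parametric assumptions, "a mixed-design model will be applied with Group (A, B, C) as a between-subject factor and Time (baseline, post-intervention) as a within-subject factor". A Group main effect is reported as well, so each group has its own baseline mean.

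On timing, section 2.1 states: "Initial assessments will be conducted before randomization and before the start of the intervention period".

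On assumptions, section 2.17 states: "Distributional assumptions will be evaluated using Shapiro–Wilk tests and visual inspection", and adds a check of variance homogeneity. If assumptions fail, the examples offered are "transformation where suitable, or mixed-model estimation with robust standard errors". No rule chooses between them. The interaction stays the focus of inference in every branch.

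Section 2.16 sizes the trial for an omnibus ANOVA and states: "A conservative medium omnibus effect size (Cohen’s f = 0.25) was adopted". It gives no baseline–post correlation, and it does not say whether f refers to the post-intervention score or to the change. Section 2.17 (missing data) intends to keep participants with incomplete follow-up under a missing-at-random assumption.

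**The concern.** Because baseline FES-I precedes randomisation, the groups have the same expected baseline and any observed difference is chance. The planned model nevertheless estimates three separate baseline means and subtracts each in full, so baseline noise passes into the treatment contrast. A model that uses the known equality is more precise at every correlation below 1.

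The second issue is pre-specification. The raw-scale model is conditional on assumption checks, and the fallback is open. FES-I has a floor of 16, and section 2.5 excludes people who use walking aids, so skew is plausible. The primary effect could then be reported in points or on a transformed scale according to what the data show.

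At stake are precision on the primary endpoint and a fixed effect measure. The validity of the trial is not in question.

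**Working it through.** **Inputs.** Section 2.16: three groups, alpha 0.05, f = 0.25, 159 evaluable, 192 recruited, losses up to 20%. Assumed, because the article does not give them: rho, and the scale of f. Equal variances at the two times are also assumed.

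**The plan's own figure.** For a one-way ANOVA, the noncentral F has lambda = N × f² and df = 2, N − 3. The smallest N for 80% power is 158, or 159 with equal groups (power 0.805). The stated 159 therefore reproduces. At 20% loss, 192 × 0.8 = 153.6, so 153 are evaluable, and the same ANOVA has power 0.788.

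**What the planned test is.** With two time points, complete data and a free Group effect, the interaction F test is identical to a one-way ANOVA on post minus baseline. With the score SD set to 1:

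- change-score variance: 2(1 − rho)
- baseline-adjusted residual variance: 1 − rho²
- ratio: (1 − rho²) / [2(1 − rho)] = (1 + rho)/2

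The ratio is 0.65 at rho 0.3, 0.75 at 0.5, 0.85 at 0.7 and 0.90 at 0.8.

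**Power at N = 153.** The adjusted model spends one further degree of freedom.

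*If f = 0.25 is on the change scale,* the change test has power 0.788 at any rho, and the adjusted model has f = 0.25 × √(2/(1 + rho)):

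| rho | Change test | Adjusted f | Adjusted model |
|---|---|---|---|
| 0.5 | 0.788 | 0.289 | 0.896 |
| 0.7 | 0.788 | 0.271 | 0.853 |
| 0.8 | 0.788 | 0.264 | 0.832 |

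*If f = 0.25 is on the post-score SD,* the change test has f = 0.25/√(2(1 − rho)) and the adjusted model has f = 0.25/√(1 − rho²):

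| rho | Change test (f) | Adjusted model (f) |
|---|---|---|
| 0.3 | 0.635 (0.211) | 0.827 (0.262) |
| 0.5 | 0.788 (0.250) | 0.896 (0.289) |
| 0.7 | 0.952 (0.323) | 0.977 (0.350) |
| 0.8 | 0.994 (0.395) | 0.997 (0.417) |

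**The assumption-check switch.** This was simulated with 53 per group and 3,000 runs per setting, for normal scores and for skewed scores confined to 16–64; both distributions are assumed. Shapiro–Wilk was applied to each of the six group-by-time cells, and any p < 0.05 triggered the switch.

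- The switch fired in 24–27% of runs with truly normal data and in 100% with skewed data.
- Type I error was 0.049–0.058 with a fixed log fallback, and 0.051–0.062 when the better of log or robust errors was taken.
- Baseline adjustment with HC3 robust errors had type I error of 0.044–0.058.
- With skewed data and a real effect (rho 0.4), power was 0.62 for the raw change test, 0.83 for the adjusted model with HC3 errors, and 0.85 for a log-scale change test. At rho 0.6 the last two were 0.91 and 0.96.

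**The case against.** The strongest defence is that nothing here is wrong. Endpoint and test agree, randomisation makes the test unbiased, and the interaction is fixed in advance. That stands: the point is about efficiency, not validity. The change endpoint does not, however, rule out adjustment, because regressing change on group and baseline gives the same group contrast as regressing the post score on group and baseline.

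Several stronger readings are tempting, and the article does not support them:

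- *That a normality test chooses the primary test.* It does not. Section 2.17 keeps the interaction in all cases. The checks, which include plots and variance tests as well as Shapiro–Wilk, select only the scale and the variance estimator.
- *That a transformation would break the 0.5 baseline SD benchmark.* Section 2.11 makes this a supplementary interpretive reference. It can be computed on raw points whatever the model scale.
- *That the switch seriously inflates false positives.* In simulation the type I error reached at most about 0.062.
- *That a single power gain can be quoted.* The gain depends on rho and on the scale of f, and neither is stated.
- *That adjustment on the raw scale always has the most power.* Under strong skew a log-scale change test did better, though for a different effect measure.

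Two further objections hold in part. The identity with a change-score ANOVA is exact only with complete data; with losses, the likelihood model departs from it, but baseline means stay unconstrained. And fallback detail often belongs in a separate analysis plan. Here, though, the article itself writes the conditional rule for the primary outcome, so the rule can be judged as stated.

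**Conclusion.** The point holds as a recommended improvement. The planned FES-I test is valid but less efficient than a model that uses the pre-randomisation baseline. The variance ratio (1 + rho)/2 is certain given equal variances and complete data; its translation into power is not. At 153 evaluable, the gain is about 11, 7 and 4 points at rho 0.5, 0.7 and 0.8 if f is on the change scale. If f is on the post-score SD, it is about 19 points at rho 0.3, 11 at 0.5, 2 to 3 at 0.7 and under 1 at 0.8. On either scale, and at every rho shown, the adjusted model keeps power above 0.80 after 20% loss.

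The open fallback is a narrower matter of pre-specification. Its cost is that the effect scale of the primary analysis may depend on the data; the cost in type I error is small.

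**What to change.** In section 2.17, name one primary model for FES-I, in points. Either of these serves:

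- post-intervention FES-I on group, adjusted for baseline FES-I; or
- the planned mixed model with one baseline mean common to all groups (Time and Group-at-post terms, no Group main effect). This keeps participants who have only a baseline, as the missing-data text intends.

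Use robust standard errors whatever the normality checks show. Keep those checks as diagnostics and any transformation as a sensitivity analysis. Apply the same baseline adjustment to the continuous secondary outcomes. State the scale of f and the assumed rho in section 2.16.

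The cost is wording and minor analysis work; no new data or participants are needed. The one trade-off is that, under strong skew, a log-scale test could have slightly more power, but for an effect that is no longer in FES-I points.
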